##### Short Healthy Eating Index

Diet quality is measured using the Short Healthy Eating Index, validated in college populations [25]. Higher scores indicate greater adherence to the Dietary Guidelines for Americans, 2020-2025 [26].

#### Physical Activity Assessments

WellNurse participants have an opportunity to engage in physical fitness training to prepare for a 5K walk or run. Before and after the training, participants complete a comprehensive measure of physical activity.

##### International Physical Activity Questionnaire

The International Physical Activity Questionnaire measures participants’ frequency of physical activity [27]. This 4-item instrument provides an overall estimate of physical activity levels over a week. The measure is valid and reliable in assessing college students’ physical activity [28].

##### Fitabase Data Collection

Participants also have an opportunity to receive a free Fitbit Versa 2 (Fitbit). Because various health indices can be derived from ongoing data collection metrics within the Fitbit, participants complete an in-person consent form separate from the WellNurse consent form before receiving their device. The WellNurse research team connects each Fitbit to the web-based database, *Fitabase*. Fitabase tracks a multitude of movement and health-related behaviors, including steps taken per day, distance traveled, calories burned per day, heart rate variability (sedentary-very active minutes, logged physical activity, floors, basal metabolic rate, and resting heart rate), and sleep behavior (minutes in light sleep, deep sleep, and rapid eye movement sleep).

#### Mindfulness-Based Stress Reduction

Participants who sign up to participate in MBSR complete additional pre- and postintervention measures.

##### Five Facet Mindfulness Questionnaire

Mindfulness is measured using the Five Facet Mindfulness Questionnaire. This survey is composed of 39 questions and five subscales, including (1) observing, (2) describing, (3) acting with awareness, (4) nonjudging, and (5) nonreactivity. This survey has demonstrated good validity and reliability in past research [29].

##### Positive and Negative Affect Scale

Participants are asked to complete the 20-item Positive and Negative Affect Scale, which measures underlying experiences of positive or negative feelings of mood or emotion. This survey has demonstrated excellent validity and reliability in past research [30].

#### Massage Therapy

##### Short Form PSS

The Short Form PSS is a 4-item perceived stress survey that demonstrates validity and reliability [31]. Participants who receive a massage are invited to complete the Short Form PSS before the massage session and again 1 week later. Additionally, they have an option to complete a qualitative question on the follow-up survey, “Describe how massage therapy has affected your stress, anxiety, or happiness. Use specific examples if possible.”

#### Attendance Records

When participants attend any additional workshop or activity, such as an exercise class, massage, or use of the WellNurse room, they sign in to track attendance.

### Interventions Under Investigation

Holistic and comprehensive interventions are under investigation that align with 4 of the National Academy of Health’s priorities areas: Priority 1: create and sustain positive work and learning environments and culture; Priority 3: support mental health and reduce stigma; Priority 6: institutionalize well-being as a long-term value; and Priority 7: recruit retain a diverse and inclusive health workforce [8].

### Environmental and System Interventions

#### Diversity, Equity, and Inclusion

According to the United States Census Bureau [32], individuals from ethnic and racial minority groups accounted for 40% of the population in 2022. Nursing programs have a responsibility to recruit and retain a more diverse student body and more diverse faculty and staff to build a vibrant nursing workforce that reflects the diversity of the population it serves [33]. Therefore, several institutional changes were implemented and are ongoing to promote a culture that embraces diversity, equity, and inclusion (DEI).

A DEI committee was established at the school in 2021. An extensive holistic admission review training was provided to the faculty and staff who interface with the admission process. A holistic admission review process was implemented that includes objective and relational admission measures. Training and workshops about diverse populations were implemented as part of routine team meetings and class presentations. Curricular experts offered courses and programming to promote faculty transforming their courses to align with Inclusive Teaching Design. Inclusive teaching is being responsive to the diversity of the class and designing learning environments that include all students while allowing students to be engaged in an equitable learning environment and feel a sense of belonging [34]. The design begins with a clear syllabus outlining tools needed for success in a course, and transparent assignment frameworks highlighting what the learner needs to do, why they need to do it, how they should do it, and how their work will be evaluated. Faculty also include an intersectionality statement in the syllabus to state their commitment to the collective diversity learners bring to the learning environment.

Classes also include a *Getting-to-Know-You Survey* before the first class meeting that identifies learner preferences and perceived barriers to learning for early intervention. The survey is used for targeted student outreach, with an initial email offering resources specific to their concerns and a frequently asked question response to all students for commonly asked questions. Building community is a focus of the first class meeting. Students introduce themselves and share pictures from their life on the learning management software discussion board. Faculty share their social identities with the class and discuss the contexts that impact learning and teaching. Vulnerability and reflexivity are essential to breaking down real and exaggerated power differentials in the course. Ground rules are discussed and published on the learning management system during the first class. A reflection prompt completed in the first meeting allows learners to consider how they manifest their nurse role. Establishing purpose with a sense of belonging and self-confidence is threaded throughout the class meetings. Holistic admissions practices and inclusive teaching strategy training from experts are incentivized among faculty and staff and ongoing.

The faculty who teach Psychiatric Mental Health Nursing implemented wellness and resilience strategies in their classrooms. Faculty provided students with several mindfulness and wellness classroom options, such as guided meditations; mindful movement and stretching; and information about campus resources before class, during times of transition, or after emotionally taxing lecture content such as suicide. Faculty also implemented short meditations before examinations and provided extra credit to engage in any of the WellNurse programming.

#### WellNurse Room

A conference room in the School of Nursing was converted to a WellNurse room. The WellNurse room signals an institutional and systemic investment in supporting the resilience of incoming students, faculty, and staff. The renovation also promotes recruitment into the MBSR program by raising the profile of these activities with dedicated space for practice.

Participants are invited to attend free workshops that aim to promote healthy behavior change through evidence-based practices. Each workshop is designed and led by an interdisciplinary member of the research team. Advertisements for upcoming workshops are posted to the School of Nursing’s social media pages and through email blasts. Attendance is optional. Workshops address various topics of concern, including the role of diet quality, sleep, and navigating test anxiety. Health behavior workshops are held monthly, both remote and in-person. Recordings are available to participants upon request.

### Classroom Enhancements

Faculty integrate selected WellNurse interventions into their classes by offering extra credit or providing assignments attached to interventions. Additionally, faculty use class time to implement short periods of mindfulness either through guided meditations, outdoor walks, or open discussion about how students might embrace mindfulness and self-care during a rigorous schedule.

### Wellness and Resilience Social Media Presence

A graduate student was hired to promote WellNurse activities and interact with students on social media. These posts highlight brief research findings about resilience, stress, and well-being among nurses and students. They also guide students through time management, test-taking strategies, community-building activities, and more.

### Mindfulness-Based Stress Reduction

MBSR is an 8-week experiential program including 2.5-hour weekly class sessions and a 1-day silent retreat. MBSR engages participants in simple evidence-based mindfulness practices, including meditation, mindful walking and movement, cognitive reframing, and communication strategies. Pioneered in 1979 by [name] at the University of Massachusetts Medical Center, MBSR includes didactic and experiential training that teaches participants to cultivate self-awareness by redirecting attention away from past or future concerns and focusing instead on the present moment. With regular practice, participants learn to change habitual stress reactivity patterns and instead more flexibly respond to stress with adaptive coping. As a result, participants learn to avoid internalizing stress in reactive patterns of negative emotion [35] and, thus, reduce distress and prevent negative health and mental health outcomes.

WellNurse partnered with the University of California San Diego School of Medicine Center on Mindfulness and Brown University Mindfulness Center to provide remote, 8-week MBSR courses via Zoom and intensive week-long, in-person MBSR courses. MBSR was offered as an elective course to count toward the students’ elective requirements for Nursing. Additionally, faculty and staff were provided work time to participate in the program. Selected WellNurse project personnel including faculty, staff, and graduate students completed a multiyear teacher training certification process through the University of California San Diego and Brown University Mindfulness Center to develop a group of certified MBSR teachers to support long-term project sustainability.

### MasterChef: Nursing Edition

This monthly workshop is innovative in combining gamified learning, cooking self-efficacy, mindful eating, and nutrition education for prelicensed nursing students. The course outline consists of (1) mindful eating concepts, (2) nutrition education, (3) participants designing their own healthful and accessible recipe, (4) participants mindfully eating and voting on their favorite meal, and (5) discussion and application to clinical practice. Participants are also encouraged to do 2 “homework” assignments per week, each emphasizing healthy eating or mindfulness behaviors. Participants also receive ingredients for recreating their healthful recipe at home and a “dorm-friendly” recipe book developed by a registered dietitian nutritionist. All students, staff, and faculty are encouraged to join, but students in designated courses receive credit for attendance.

### Fitness Interventions

Participants are eligible to receive a free Fitbit Versa 2. Fitness trainers provide weekly 5K training in the fall and spring semesters to prepare participants for a 5K walk or run. Additionally, the campus recreation center offers nursing-specific fitness courses such as yoga and full-body workouts to promote a fitness community. Faculty are integrating fitness step challenges using the Fitbit devices as part of class assignments.

### Ethics Approval

The University of Maine institutional review board reviewed and approved the WellNurse research project procedures (02-05-2-2022).

## Results

### Overview

The project was funded on January 1, 2022. Data collection started in March 2022. A total of 267 participants have been recruited. Results will be published after each semester starting in December 2023.

The primary study variables will be analyzed 4 times per year to track population outcomes and changes. Regression analysis will be conducted to examine the relationship of students’ on-time progression, stress, resilience, and burnout with physical and emotional health variables and on-time progression. Subanalysis will be conducted for unique groups such as first and fourth year students, faculty and staff, and graduate students, as well as students from historically underrepresented populations such as first-generation college students and racial and ethnic minorities. Additionally, program retention, on-time graduation, and faculty and staff retention will be tracked over time. The cost of implementing MBSR, massage therapy, MasterChef, and fitness events will be tracked to determine cost per student. Additionally, feasibility will be measured using qualitative focus group interviews with students who complete specific interventions along with attrition rates for completing specific interventions such as MBSR and MasterChef.

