**Results:**

The project was funded on January 1, 2022. Data collection started in March 2022. A total of 267 participants have been recruited. Results will be published after each semester starting in December 2023. WellNurse evaluation follows the Rapid Cycle Quality Improvement framework to continuously monitor ongoing project processes, activity outcomes, and progress toward reducing burnout and increasing resilience. Rapid Cycle Quality Improvement promotes the ability to alter WellNurse interventions, examine multiple interventions, and test their effectiveness among the nursing education population to identify the most effective interventions.

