### MasterChef Analysis

MasterChef will be evaluated initially for feasibility through a qualitative focus group design along with an expert content analysis. After modifications to the program based on feasibility analysis, the intervention will be evaluated using a matched-based cohort design with the non-MasterChef control group selected based on gender, ethnicity, and year in college matched-based design, with a focus on gender, ethnicity, and year in college. Descriptive and frequency statistics were used to analyze the sample’s baseline and demographic data. A 2-way repeated-measures analysis will be used to assess significant changes in baseline and postintervention outcomes within the experimental group and as a comparison with the control. Participants will complete the aforementioned nutrition measures before the week-long Fall 2023 program delivery, directly after the program, and again at the end of the semester. A control will be recruited through a matched-based design. A 2-way repeated-measures ANOVA will be used to identify significant changes between baseline data, postintervention data, and follow-up data between the intervention and control group. The program will also be implemented in the format of monthly workshops. A multivariate ANOVA will be used to compare health outcomes between curriculum formats. Multiple linear regressions will be used to identify predictors of diet quality using the combined fall and spring samples. Significance levels will be set at *P*<.05.

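### The interview part of feasibility samples only students who finish an intervention, so no described source records participants' reasons for not finishing

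*Protocol article*

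**What the plan says.** The protocol article deals with feasibility in two places.

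- **Results, Overview.** One sentence names two measures, interviews and attrition: "feasibility will be measured using qualitative focus group interviews with students who complete specific interventions along with attrition rates". The second measure reads in full "attrition rates for completing specific interventions such as MBSR and MasterChef".
- **Results, MasterChef Analysis.** "MasterChef will be evaluated initially for feasibility through a qualitative focus group design along with an expert content analysis". The matched-cohort evaluation then follows "After modifications to the program based on feasibility analysis". This section does not say again who sits in the focus groups.

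The intervention section on MasterChef gives context on who takes part: "All students, staff, and faculty are encouraged to join", and "students in designated courses receive credit for attendance".

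**The concern.** A feasibility assessment asks whether people can take up and finish an intervention and, if not, what stops them. Choosing interviewees because they finished conditions on the outcome in question. Finishers can describe difficulties they overcame. They cannot report what made someone else stop.

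At stake is the information used to change MasterChef. If barriers that led people to stop are heard only second-hand, the changes may be tuned to those who coped with the existing format, and the modified version is the one that goes forward to comparative evaluation. The same gap affects MBSR, which the article describes as eight weekly sessions of 2.5 hours plus a one-day retreat, or an intensive week. The article itself names academic workload as a source of students' stress, so reasons for stopping such a programme are worth having.

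**Working it through.** No arithmetic applies. The article gives no attrition rate, focus-group size or feasibility threshold, and its only sample figure is the 267 participants recruited overall. The check is whether any described source records, from participants, why they did not complete an intervention.

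**Sources named as feasibility measures**

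1. *Focus groups (Overview).* Participants speak in their own words, but the stated frame is students who finish. Non-completers are not invited under this wording.
2. *Attrition rates (Overview).* Non-completers are counted, with MBSR and MasterChef named. A rate carries no reasons.
3. *Expert content analysis (MasterChef Analysis).* This is expert judgement of the programme, not participants' accounts.

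**Other sources that might fill the gap**

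4. *Comprehensive Wellness Survey.* It goes to participants in weeks 4 and 14 whether or not they complete an intervention. The listed content is demographics, grade point average, progression, stress, life satisfaction, burnout, resilience, body mass index and sleep. No item on reasons for stopping is listed.
5. *MBSR pre- and post-assessments (MBSR Analysis).* The second assessment follows the final session, so it too is tied to reaching the end. The added measures cover mindfulness and affect.
6. *Number of MBSR sessions attended (MBSR Analysis).* This is planned as a dose variable for later models. It shows partial attendance, not its cause.
7. *Attendance Records.* Sign-in shows who came, not why others did not return.
8. *Open question on massage (Massage Therapy).* It is optional, goes only to people who had a massage, and asks about effects on stress, anxiety or happiness.
9. *Nutrition measures for MasterChef.* They are taken before the programme, directly after it and at the end of the semester. They cover eating, cooking, body image and diet, not reasons for leaving.

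**Result.** Items 2, 6 and 7 can show that someone left or attended in part. Items 1 and 8 let participants speak freely, but the first is limited to finishers and the second asks a different question about a different intervention. None of the nine gives participants' reasons for not completing.

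**Link to MasterChef.** The Overview states the finisher rule generally and names MasterChef in the same sentence, for attrition. The MasterChef Analysis section gives no other rule. That the MasterChef groups are made up of finishers is therefore the natural reading, but it is an inference. Course credit for attendance in designated courses may also influence who finishes.

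**The case against.** A reader might infer more than the article supports, in four ways.

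- **That non-completers are left out of feasibility altogether.** They are not. The sentence that limits the interviews also sets attrition rates as a measure. Non-completers are counted but not interviewed.
- **That the MasterChef redesign rests only on a one-sided sample.** The MasterChef Analysis section adds an expert content analysis, and it does not restate who joins the focus groups.
- **That barriers to completion will go entirely unheard.** Finishers can meet the same barriers and report them. What is missing is the account of the people who stopped.
- **That every rapid-cycle change depends on these interviews.** The abstract says the quality-improvement framework "promotes the ability to alter WellNurse interventions", but ties this to monitoring of processes, outcomes and progress. It does not say that changes are drawn from the focus groups.

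These points stand and narrow the concern. It is also fair that feasibility is a supporting assessment: the comparisons of burnout, stress and resilience do not depend on it.

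One further objection carries less weight. The article condenses a fuller protocol, which may contain exit procedures. That would be a full answer if the article were silent on who is interviewed. It is not silent: it states a sampling rule, and the rule as stated is the wrong one for the purpose. If the full protocol already provides for non-completers, the article's sentence should say so.

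**Conclusion.** The point holds in a limited form. The qualitative part of feasibility is restricted to students who finish, attrition rates cannot supply reasons, and nothing else described in the article does so. The participant input to the MasterChef modifications therefore probably comes from finishers only, alongside expert review.

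The size cannot be estimated from the documents. It grows with the share who do not complete and with how far their reasons differ from the difficulties that finishers report, and neither is given. Focus groups yield themes rather than proportions, so a percentage bias would not describe what the plan sets out to measure.

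The conclusion rests on two assumptions: that the general rule in the Overview also governs the MasterChef groups, and that no exit procedure exists beyond what the article describes. No outcome analysis is invalidated. The change is worth making because a programme is modified on this information.

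**What to change.** In the Overview under Results, change the focus-group rule to students who registered for or started the intervention, including those who did not complete it. Offer non-completers of MBSR and MasterChef either a focus-group place or a web form of two to three questions on why they stopped. Report their themes separately from finishers' themes, and do so before MasterChef is modified. In the MasterChef Analysis section, state that the same rule applies.

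**Finding the people.** For MasterChef, the web-based registration form required before the workshop (Nutrition Assessments), set against attendance records, would identify them. That form covers only the cooking workshop, and the examples under Attendance Records do not name MBSR. For MBSR, the source would be the count of sessions attended, which the MBSR Analysis section already plans to use. The team should confirm that it is recorded for people who stop early.

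**Cost.** One change of wording, some further invitations and a short form. No comparison group, sample size or statistical model changes. The drawback is that non-completers will respond less often than finishers. The short form reduces this but does not remove it, so the number invited and the number who answered should be reported with the themes.
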